### Strategy coordination

The phased timeline for these strategies is designed to be realistic and manageable for clinicians in a busy primary care setting. The activities are staggered, with promoter identification taking place first, followed by a more gradual rollout of thematic training and exchange sessions to avoid overwhelming staff and to facilitate effective skill building over time.

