		Clinician provides a referral	IOF: Fidelity RE-AIM: Implementation	From the fifth step in the BISC implementation steps in the China Clinical Cessation Guidelines (2015 edition), indicating whether the clinician referral patient to smoking cessation clinic.	Quantitative data, dichotomous variable (0,1)	Questionnaire	USP visit/telephone callback^b^		●	●	●	●
		Coverage of BISC delivery	IOF: Penetration RE-AIM: Reach	Percentage of patients who received BISC as compared to the patients who attended to PHC.	Quantitative data, percent (0–100%)	Questionnaire	USP visit/telephone callback^b^		●	●	●	●
	Tertiary outcome	Applicability of BISC delivery	IOF: Feasibility	The extent to BISC can be successfully carried out within PHC clinician.	Quantitative data 0–100 points	NPT questionnaire	Questionnaire survey				●	
		Acceptance of BISC delivery	IOF: Acceptability REAIM: Adoption, Maintenance	The perception among the PHC facilities that BISC implementation techniques is agreeable, palatable, or satisfactory.	Qualitative data	Interview outline	Semi-structured interview				●	
			IOF: Adoption RE-AIM: Adoption	The intention, initial decision, or action to try or employ BISC from the perspective of the PHC facilities.							●	
			IOF: Appropriateness RE-AIM: Adoption	The perceived fit, relevance, or compatibility of BISC for the PHC facilities; and/or perceived fit of BISC to address a particular issue or problem.							●	
		Sustainability of BISC delivery	IOF: Sustainability RE-AIM: Adoption, Maintenance	The possibility to BISC is maintained or institutionalized within PHC clinician’s ongoing, stable operations.	Quantitative data	The Program Sustainability Assessment Tool (PSAT)	Questionnaire survey				●	
		Sustainment of BISC delivery	IOF: Sustainability; RE-AIM: Maintenance	The continued implementation of BISC by the primary care clinician over time.	Quantitative data and qualitative data	The Provider Report of Sustainment Scale (PRESS) and interview outline	Questionnaire survey and semi-structured interview					●
		Cost of BISC delivery	IOF: Implementation Cost RE-AIM: Implementation	The cost of implementation, depends upon the costs of the BISC implementation techniques.	-	Administrative data					●	
**Effectiveness outcomes**	Secondary outcome	7-day point abstinence status		Self-reported abstinence from smoking for the past 7 days.	Quantitative data and qualitative data	-	Telephone callback			●	●	●

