		Daily cigarette consumption		Number of cigarettes smoked daily. To assess a reduction in smoking behavior.	Quantitative data and qualitative data	-	Telephone callback			●	●	●
	Tertiary outcome	Patient satisfaction with the BISC provided by the clinician		The patient’s perceived satisfaction with how the physician implemented BISC during the consultation.	Quantitative data and qualitative data	-	Telephone callback			●	●	

a I: Enrolment. II: Baseline (i.e. before the first of BISC implementation). III: Mid-term (i.e. at the middle of BISC implementation), which will be executed the weeks 1, 3, 5, 7, 9 and 11 after the start of the BISC implementation. IV: Endline (i.e. at the end of BISC implementation). V: Follow-up (i.e. maintenance of the BISC), which will be executed 6 months after the endline.

b Data collection via telephone callbacks with patients in periods I and V; Data collection by USP visits in period IV. IOF: Implementation Outcomes Framework. BISC: brief intervention for smoking cessation. USP: unannounced standardized patient.

*Outcomes*

The study outcomes will be aligned with the principles of Proctor’s Implementation Outcomes Framework (IOF) and the RE-AIM framework. According to the type 3 hybrid design, the outcomes are categorized into primary and secondary aims to reflect the dual focus on implementation strategies and patient-level effects.

Primary aim: implementation outcomes

The primary aim of this study is to evaluate the effectiveness of the implementation strategies. These outcomes will be assessed by a combination of methods to ensure a comprehensive evaluation.

The primary outcomes, ‘clinician ask smoking status’ and ‘clinician advise to quit’, will be assessed using unannounced standardized patient (USP) visits. These outcomes serve as key measures of fidelity to the brief intervention protocol. The secondary outcomes, ‘clinician ask about number of cigarettes smoked’, ‘clinician discuss the harms and benefits of quitting’, and ‘clinician provide a referral’, will also be measured using a combination of USP visits for clinicians and telephone callbacks for outpatients.

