The secondary aim of this study is to assess the effects of the BISC intervention on patient-level outcomes. These outcomes will be measured via a patient phone call survey at two distinct time points. At the end of the intervention, a phone call will be made to all patients who were identified as smokers and received the BISC intervention during the study period. This initial survey will assess their smoking status immediately following the intervention and confirm their receipt of the BISC components. A 6-month follow-up survey will then be conducted exclusively with patients who self-reported as smokers and received the BISC intervention. This survey will assess the long-term effectiveness of the intervention by measuring key indicators, including 7-day point abstinence status, daily cigarette consumption, and patient satisfaction with the BISC provided by the clinician. A summary of all outcome measures, their respective assessment methods, and time points is presented in Table 2.

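### Patient smoking calls are timed from trial milestones, not from each patient's consultation, so time since advice varies by up to the whole implementation period and some endline 7-day answers straddle the advice

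*Protocol article*

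**What the plan says.** Under Secondary aim: effectiveness outcomes, the timing is: "These outcomes will be measured via a patient phone call survey at two distinct time points". When the intervention ends, "a phone call will be made to all patients who were identified as smokers and received the BISC intervention during the study period". The stated purpose is: "This initial survey will assess their smoking status immediately following the intervention and confirm their receipt of the BISC components". Then: "A 6-month follow-up survey will then be conducted exclusively with patients who self-reported as smokers and received the BISC intervention", with the aim of "measuring key indicators, including 7-day point abstinence status, daily cigarette consumption, and patient satisfaction with the BISC provided by the clinician".

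Table 2 defines the abstinence outcome as "Self-reported abstinence from smoking for the past 7 days" and marks it at three periods: mid-term, endline and follow-up. Footnote a places endline at the end of implementation and follow-up six months after endline. Of the mid-term period it says: "which will be executed the weeks 1, 3, 5, 7, 9 and 11 after the start of the BISC implementation".

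Strategy coordination says of the techniques: "The activities are staggered, with promoter identification taking place first". The patient covariates listed under Data analysis are gender, age, primary diagnosis and smoking status. Time since advice is not among them.

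**The concern.** Advice can be given at any point during implementation, but every call date is a trial date. At one endline call, a patient advised in the first week and a patient advised the day before answer the same question at very different distances from the advice. The stated purpose of capturing smoking status straight after the intervention is then met only for patients advised late. For those advised in the last few days, the recall period includes days before they were advised.

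Abstinence after brief advice generally changes with time. If the techniques shift when advice is given, conditions are compared at different average times since advice, and abstinence and daily consumption could differ even where advice works equally well. Randomization does not remove this, because the timing of advice is itself a consequence of the assigned technique.

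**Working it through.** The plan states no figure on this point, so there is none to reproduce. The check is calendar arithmetic.

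**Inputs from the protocol**
- Last mid-term wave: week 11 (Table 2, footnote a).
- Endline: end of implementation, no week number (same footnote).
- Follow-up: six months, about 26 weeks, after endline (same footnote).
- Study dates: January to December 2026 (Study setting), about 52 weeks.

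**Assumed.** Implementation length D is not stated. A lower value of about 12 weeks is inferred from the week-11 wave. If follow-up must fit within 2026, the upper value is 52 − 26 = 26 weeks.

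**1. Time since advice.** For advice at time s (weeks), the lag at endline is D − s and at follow-up 26 + (D − s).

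| D (weeks) | Lag at endline | Lag at follow-up |
|---|---|---|
| 12 | 0–12 | 26–38 (about 6–9 months) |
| 26 | 0–26 | 26–52 (about 6–12 months) |

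**2. Share at endline with lag under 7 days, even delivery.** This is 1/D: 1/12 = 8.3% and 1/26 = 3.8%. For these patients the 7-day period starts before the advice and ends after it. It lies wholly before the advice only if the call falls on about the day of the consultation. At follow-up the lag is at least 26 weeks, so the share is 0%. At the mid-term calls it can occur, but the protocol does not say which patients each wave calls, so no share can be given.

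**3. Can the lag differ by condition?** The documented start times are:
- Incentives: training within the first week, a directive within 24 hours of it, then weekly checks.
- Champions: recruitment within the first week, then interviews, appointment and cultivation, with no duration given for selection.
- Education: daily reinforcement from week 1, workshops from the first month, peer exchange from week 8.

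Every technique has activity from the first week, but intensity builds differently. The lag can differ by condition; nothing in the protocol shows that it does.

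**4. Possible size, on assumptions only.** Let abstinence be 0 for a lag t under 1 week and p0 × 0.5^((t − 1)/h) afterwards. Take (p0, h) as (8%, 8 weeks), (10%, 4 weeks) and (6%, 12 weeks). Let delivery density be proportional to 1 + k(2s/D − 1) in a late-weighted condition and 1 − k(2s/D − 1) in an early-weighted one. Mean lags are D/2 − kD/6 and D/2 + kD/6. The advice works equally in both. Results are late minus early, in percentage points, in the order of the three (p0, h) pairs.

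| Setting | Mean lags (weeks) | Spurious difference |
|---|---|---|
| Endline, D = 12, k = 0.25 | 5.5 vs 6.5 | 0.14, 0.39, 0.03 |
| Endline, D = 12, k = 1 | 4 vs 8 | 0.57, 1.57, 0.11 |
| Endline, D = 26, k = 0.25 | 11.9 vs 14.1 | 0.45, 0.55, 0.28 |
| Endline, D = 26, k = 1 | 8.7 vs 17.3 | 1.79, 2.21, 1.13 |
| Follow-up, D = 12, k = 1 | 30 vs 34 | 0.19, 0.04, 0.23 |

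With k = 1, delivery starts at zero in one condition and falls to zero in the other. That is an outer bound which no section describes. With k = 0.25 the endline difference is 0.03 to 0.55 points.

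**5. Text against Table 2.** The text has two call points and names 7-day abstinence only at the six-month survey. Table 2 marks it at mid-term, endline and follow-up, with six mid-term waves.

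**The case against.** **A reader might infer that time since advice does differ by condition.** The case for this points to the early directive and the week-8 peer exchange. It leaves out that education also has daily activity from week 1 and that champion recruitment falls in the first week. The documents support only that it can differ.

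**A reader might infer a sizeable bias.** The larger figures come from opposite extreme delivery shapes in two single conditions. A factorial main effect averages four conditions against four, and the decay model has no source in the protocol. This objection stands: the size is not computable, and moderate shifts give small differences.

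**A reader might infer that the 7-day period precedes the advice, or that the long-term result is affected in the same way.** For nearly all affected patients it straddles the advice. At six months, the only survey where the text names 7-day abstinence, it falls wholly after the advice. Both corrections stand. What remains at that call is the spread in lag.

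**The outcomes are secondary.** The primary outcomes come from standardized-patient visits and are untouched. The factorial analysis is described for adherence to BISC practices. This limits the consequence.

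**A condensed article may leave call windows and lag adjustment to fuller documents.** This is fair for windows and adjustment. The anchor, however, is stated here, and it is a trial milestone. An analysis plan cannot re-time calls already made.

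**Conclusion.** The point holds as a problem of call timing. Both the text and Table 2 fix the patient calls to trial milestones. Time since advice at endline spans 0 to about 12 weeks (inferred length) or at most about 26 (calendar limit), and the nominal six-month call falls about 6 to 9 months after advice, up to 12. The aim of measuring smoking status straight after the intervention is not met for patients advised early. With even delivery, about 8% of endline answers (12 weeks) or 4% (26 weeks) straddle the advice. The same can happen at the mid-term calls in Table 2, but not at six months.

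Bias between conditions is possible, because activities are staggered, but it is not demonstrated. It is probably small under moderate differences in delivery timing. The primary outcomes are unaffected. The change is worth making because it is cheap now and cannot be made once the calls are done.

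**What to change.** - Anchor the effectiveness calls to the patient's own consultation date in all conditions: one at a fixed interval longer than 7 days, with a stated window, and one at 6 months after the consultation.
- Do not use a 7-day abstinence answer obtained within 7 days of the consultation.
- Reconcile the effectiveness text (two call points) with Table 2 (mid-term, endline and follow-up), and state which patients, if any, the mid-term waves call for smoking outcomes.
- If calendar-based calls stay, record each consultation date and report time since advice by condition. Adjust for it only in a sensitivity analysis, because it arises after randomization and may be affected by the technique.

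Cost: protocol wording and a rolling call list, with about the same number of calls. The downside is that first calls are spread over the implementation period instead of made in one batch. The last six-month calls need not fall later than now: a patient seen on the last day of implementation would be called six months after endline under either rule.

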## METHODS

### Study design

*Hybrid and full factorial design*

This study is designed as a type 3 hybrid implementation trial^14^, concentrating on the development and assessment of the effectiveness of a specific implementation strategy to enhance the adoption and implementation of BISC. The design prioritizes the evaluation of implementation strategies while also examining clinical outcomes. The research adheres to the principles of the Multiphase Optimization Strategy (MOST)^15,16^ with its core component being a 2×2×2 full factorial design (Figure 1). This design will result in eight distinct experimental conditions and allows for the evaluation of the main effects and potential interaction effects of the implementation techniques, which is the core purpose of the optimization trial. The study has identified four key implementation techniques to be included in the trial. One of these, assessing readiness and identifying barriers and facilitators, will be included as a constant component in all eight conditions, ensuring a foundational level of support for all participants. The remaining three techniques serve as the three factors of the factorial design, each with two levels (present or absent) (Table 1).

**Table 1 T0001:** Full factorial design (2×2×2) with constant components within a type 3 hybrid effectiveness-implementation trial of BISC in primary healthcare facilities with a sample of 640 clinicians, Guangdong, China, January 2026 – December 2026

*Experiment* *conditions*	*Constant component*	*Optional components to be tested*		
	*Assess for readiness and* *identify barriers and* *facilitators*	*Identify and prepare* *champions*	*Alter incentive/allowance* *structures*	*Conduct educational* *meetings*
1	Yes			
2	Yes	Yes		
3	Yes	Yes	Yes	
4	Yes	Yes		Yes
5	Yes		Yes	
6	Yes		Yes	Yes
7	Yes			Yes
8	Yes	Yes	Yes	Yes

Yes: means included in intervention. No: means not included in intervention. The specifics form (such as ‘ranking primary healthcare clinicians’ execution of BISC and providing spiritual rewards for excellence’) of each component (such as ‘Alter incentive/allowance structures’) will be developed by inviting stakeholders to work together, following the principles of co-production. BISC: brief intervention for smoking cessation.

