**Figure 2 F0002:**
[figure not shown]
Sampling procedure of primary healthcare facilities with 640 clinicians, Guangdong Province, China, January 2026 – December 2026

In the second stage, all primary healthcare institutions under the jurisdiction of the recruited local health authorities in these three cities will be included in the sampling frame. These institutions will then be regrouped into PSUs based on the number of clinicians. This ensures that each unit has a sufficient number of clinicians, preventing the exclusion of smaller institutions from the sampling process. The PSUs will then be sampled using a probability proportional to size (PPS) sampling method.

The study will be conducted as a cluster-randomized trial. The intervention will be delivered to the entire cluster (PSU), but the intervention’s effect will be measured at the clinician level. The measurement is based on the average performance of a random sample of clinicians within the cluster. This is achieved through unannounced standardized patient (USP) visits, which function as the final step of the sampling process. A minimum of 80 USP visits will be assigned to each experimental condition.

*Sample size and power*

Power analyses were conducted to determine the sample size needed to test the effect of the implementation strategies on our primary outcome, ‘clinician advice to quit’. The detailed definition and measurement of this outcome are provided in the section on study outcomes. Based on prior research, the baseline rate for this outcome was 33.9%^13^. Through stakeholder consultation, it was determined that a 40% increase in delivery, resulting in a final primary outcome of 47.46%, would be considered a clinically meaningful effect. Assuming a two-tailed test with an alpha level of 0.05 and a desired power of 0.8, a sample size of 28 participants per cluster is required. Accounting for the cluster-randomized design with a design effect (Deff) of 2 and adjusting for an anticipated 20% loss to follow-up, the sample size has been intentionally increased to further enhance statistical power for detecting higher-order interactions. Consequently, the required sample size for one experimental condition is approximately 80 participants. Given our study design with eight conditions (one condition per PSU, for a total of eight PSUs), this translates to 640 participants in total.

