### Data analysis

*Quantitative analysis*

Data will undergo de-identification prior to analysis. Baseline characteristics of participants will be presented, utilizing mean and standard deviation for continuous variables and frequency and percentage for categorical variables. The trial outcome analysis will adhere to the intent-to-treat principle. Generalized estimating equations (GEE) with a binomial distribution and log link function will be used for the primary binary outcome, with clustering specified at the PSU level, to assess the main and interaction effects of the four implementation techniques on adherence to BISC practices among primary healthcare clinicians. The model will account for robust predictors of outcomes, including baseline adherence scores and sociodemographic factors of clinicians^24-26^. Effect coding will be applied to each experimental condition, and subgroup analyses based on age, gender, clinician level, and facility will be conducted to further explore the impact of different technique combinations on BISC implementation. Sensitivity analyses, involving imputation of missing values through random forest, will be performed to validate the robustness of the findings^27^. For continuous outcomes, GEE models with a Gaussian distribution and identity link function will be employed, adjusting for the same covariates and clustering at the PSU level. In the analysis, control for covariates including clinician-related information (gender, age, professional title, and department) and patient-related information (gender, age, primary diagnosis, and smoking status). We will perform subgroup analyses on patient smoking status, level of tobacco dependence, and clinician department to investigate differences in BISC implementation among different types of clinicians for various types of patients.

Hypothesis tests will be two-sided, with statistical significance set at p<0.05. All statistical analyses will be performed using Stata version 16.0 and R version 4.5.2.

*Qualitative analysis*

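### Abstinence and daily cigarettes are collected at endline and 6 months only from patients who received BISC, so any comparison by condition is selected after randomization and the stated aim has no comparator

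*Protocol article*

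**What the plan says.** The protocol article, Study variables, under the secondary aim on effectiveness outcomes, states: "The secondary aim of this study is to assess the effects of the BISC intervention on patient-level outcomes". Two telephone surveys serve this aim.

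- Endline: "a phone call will be made to all patients who were identified as smokers and received the BISC intervention during the study period".
- Six months later: a survey "conducted exclusively with patients who self-reported as smokers and received the BISC intervention", with indicators "including 7-day point abstinence status, daily cigarette consumption, and patient satisfaction with the BISC provided by the clinician".

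Table 2 lists abstinence and daily cigarette consumption as secondary effectiveness outcomes, obtained by telephone callback. It marks them at mid-term (period III) as well as at endline and follow-up, but names no population for the mid-term calls. The text names only the two time points above.

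Three other statements bear on the point.

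- Study design gives the purpose of the strategies as "to enhance the adoption and implementation of BISC".
- Table 2 makes receipt of BISC an outcome in its own right, coverage: "Percentage of patients who received BISC as compared to the patients who attended to PHC".
- Data analysis, Quantitative analysis, states: "The trial outcome analysis will adhere to the intent-to-treat principle".

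**The concern.** The techniques are randomized to clusters and are meant to change how many smokers are advised. A technique can help smokers quit by getting more of them advised. A survey that admits only recipients takes that route out of the comparison, because each condition is then judged only on the patients it managed to reach.

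The recipients also differ between conditions. Where a technique works, they include smokers who would otherwise have gone unadvised, and the other conditions have no counterpart for these patients. If those smokers are more or less ready to quit than the rest, the comparison is biased.

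The aim as worded fails separately. It asks for the effect of BISC on patients, and no unadvised smoker is surveyed at endline or at 6 months.

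This is a rule about data collection. Outcomes that are never collected from unadvised smokers cannot be recovered by a later analysis.

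**Working it through.** **Inputs from the protocol article (Sample size and power).** For advice to quit, "the baseline rate for this outcome was 33.9" per cent. The target is a 40% relative increase: 33.9% × 1.4 = 47.46%, which reproduces the stated figure. The article gives no quit rate and no sample size for the patient outcomes, so there is no planned figure for them to reproduce.

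**Assumptions.** (a) The advice rate stands in for receipt of BISC. (b) A technique causes no smoker to go unadvised. (c) All quit rates below are assumed.

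**Step 1: who is surveyed.** Divide smokers into three groups:
- A, advised with or without the technique: 33.9%
- C, advised only with the technique: 47.46% - 33.9% = 13.56%
- N, not advised in either case: 100% - 47.46% = 52.54%

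Without the technique the survey contains A only. With it, the survey contains A and C, and C makes up 13.56 / 47.46 = 28.6% of it.

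**Step 2: what the two comparisons estimate.** Let a, c and n be the quit rates of the three groups without advice, and e the points that BISC adds.
- Recipients only, absent: a + e
- Recipients only, present: [33.9(a + e) + 13.56(c + e)] / 47.46
- Difference among recipients: 0.2857 × (c - a). The BISC effect e cancels.
- Difference among all smokers: 0.1356 × e. Only C changes status.

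**Step 3: numbers, with n = 3% and e = 5 points.**

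| a | c | Recipients, absent | Recipients, present | Difference | All smokers, absent | All smokers, present | Difference |
|---|---|---|---|---|---|---|---|
| 8% | 3% | 13.00% | 11.57% | -1.43 | 6.39% | 7.07% | +0.68 |
| 5% | 5% | 10.00% | 10.00% | 0.00 | 5.64% | 6.32% | +0.68 |
| 3% | 8% | 8.00% | 9.43% | +1.43 | 5.37% | 6.05% | +0.68 |

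With e = 2 points the all-smokers difference is 0.1356 × 2 = +0.27; with e = 0 it is 0. The recipients-only differences do not move. They reflect who was reached and carry no information on whether advice works.

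**Step 4: precision of the unselected comparison.** Suppose advice raises quitting from 3% to 6% in every smoker.
- Absent: 0.339 × 6% + 0.661 × 3% = 4.02%
- Present: 0.4746 × 6% + 0.5254 × 3% = 4.42%
- Recipients only: 6% in both

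For 80% power at two-sided 0.05, the number per factor level is 7.849 × (0.0402 × 0.9598 + 0.0442 × 0.9558) / 0.00407². With unrounded rates this is about 38,000 smokers, before any design effect.

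**The case against.** **No comparison of abstinence by condition is expressly planned.** The aim refers to the effect of BISC, and the only factorial model set out in detail concerns clinician adherence. This stands in part: the article gives no separate model for abstinence. However, the intention-to-treat sentence covers the trial outcome analysis in general, and the Gaussian model for continuous outcomes could take in cigarettes per day. If no comparison is intended, the aim still has no comparator.

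**These are secondary outcomes in a type 3 hybrid.** This stands. Asking and advising are measured by standardized-patient visits, where receipt of BISC selects no one. A reader might infer that the primary conclusions are compromised; nothing in the document supports that.

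**The direction of bias is unknown.** This stands. A reader might infer that better techniques will look worse. The table shows that the sign turns on who is additionally reached, and the document gives no quit rates.

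**Other callbacks are broader.** A reader might infer that coverage becomes 100% by construction. Table 2 defines coverage against all attendees and schedules it from baseline, and the text mentions callbacks to outpatients, so a wider call stream seems intended there. That stream is not applied to the effectiveness outcomes at endline or 6 months.

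**Who identifies smokers is not stated.** A reader might infer that both primary outcomes define the call list. The article does not say that identification rests on the clinician asking, and the 6-month sentence refers to self-report. Selection on receipt of BISC is explicit and is enough for the point.

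**An unselected comparison would have little power.** This stands (step 4), and it bears on how the result should be reported.

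**Conclusion.** The point holds for the endline and 6-month surveys. Abstinence and daily cigarettes are collected in a subset defined by what the techniques are randomized to change. A comparison of them by condition is not intention-to-treat, can be biased either way and misses any benefit from wider reach. The effect of BISC on patients has no comparator.

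At the planned rates, 28.6% of recipients under an effective technique have no counterpart without it, provided that the technique prevents no advice and that the advice rate represents receipt of BISC. The range of -1.43 to +1.43 points against +0.68 illustrates the mechanism under assumed quit rates and is not a forecast.

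The remedy has to be in place before the calls are made. The population of the mid-term calls in Table 2 is unstated; it does not rescue the two surveys that the text defines.

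**What to change.** 1. For abstinence and cigarettes per day, draw the call list from outpatient attendance in each PSU, extending the outpatient callbacks already planned for fidelity and coverage. Include every patient sampled who reports having smoked at the time of the visit, whether or not the clinician asked or advised.
2. Analyse these outcomes by assigned condition, and report the contrast as an estimate with its confidence interval.
3. Keep recipients-only results, including satisfaction, as descriptive.
4. State the mid-term population in Table 2 and reconcile it with the two time points in the text.

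**Cost.** The number of calls can stay fixed by sampling, but many will reach non-smokers. If outpatients smoked at the 27.7% adult rate for 2015 quoted in the Introduction (an assumption), 100% - 27.7% = 72.3% of calls would do so. The contrast in abstinence will be small and imprecise.

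**If the call list cannot be changed,** restate the secondary aim as a description of smoking outcomes among BISC recipients, and claim no effect of BISC or of the techniques on smoking.

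### The 6-month survey's entry rule, most naturally read, leaves out patients who had stopped smoking by the end-of-intervention call, so 6-month abstinence would miss sustained quitters.

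*Protocol article*

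**What the plan says.** Under the secondary aim, the Protocol article sets out two patient telephone surveys. For the first, held once the intervention has finished, the article plans as follows: "a phone call will be made to all patients who were identified as smokers and received the BISC intervention during the study period". Its content is given next: "This initial survey will assess their smoking status immediately following the intervention and confirm their receipt of the BISC components". The second survey follows: "A 6-month follow-up survey will then be conducted exclusively with patients who self-reported as smokers and received the BISC intervention". Its purpose is to show long-term effectiveness by "measuring key indicators, including 7-day point abstinence status, daily cigarette consumption, and patient satisfaction with the BISC provided by the clinician".

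Table 2 lists 7-day abstinence as a secondary effectiveness outcome, defined as "Self-reported abstinence from smoking for the past 7 days", collected by telephone callback and marked at mid-term, endline and follow-up. The table's footnote fixes the last of these: "V: Follow-up (i.e. maintenance of the BISC), which will be executed 6 months after the endline". The table names no population for any of the three periods. The Data analysis section adds: "The trial outcome analysis will adhere to the intent-to-treat principle".

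**The concern.** A cessation outcome needs a cohort fixed by smoking status before follow-up begins. Here the second survey's population is described by a self-report of smoking, immediately after a call that asks treated smokers whether they still smoke. If that answer decides who is called again, the follow-up selects on the outcome it is meant to measure. A patient who quit early and stayed abstinent is the best result the intervention can produce, and that patient would be in neither the numerator nor the denominator at 6 months. Relapse among early quitters could not be estimated either. Daily cigarette consumption, collected in the same survey, would lose the same patients.

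This is not a detail that can wait for an analysis plan. The article itself states who is called, and no later analysis can recover a 6-month status that was never collected.

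**Working it through.** **Reading the text.** The article gives no figure for 6-month abstinence, so there is nothing to reproduce. The first check is of wording.

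| | End-of-intervention call | 6-month survey |
|---|---|---|
| Smoking condition for entry | patient had been identified as a smoker | patient self-reported being a smoker |
| BISC condition for entry | received BISC | received BISC |
| Recorded | smoking status after the intervention; receipt of BISC | 7-day abstinence, cigarettes per day, satisfaction |

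Three features point to the first call as the filter.
- The two entry conditions of the second survey match, in order, the two items the first call records.
- The wording moves from identification as a smoker to self-report.
- The second survey is introduced as a subsequent and exclusive step. If self-report meant status at the index visit, the rule would narrow the first cohort little or not at all.

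Nothing in the article ties the self-report to the index visit, or says that patients abstinent at the first call are still contacted.

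**Size, under assumptions.** Let q be the proportion abstinent at endline, r the proportion of those who relapse by 6 months, and L the proportion of endline smokers who quit later. None of the three is in the article.

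- 6-month abstinence in all treated smokers: q(1 − r) + (1 − q)L
- 6-month abstinence in endline smokers only: L
- Share of 6-month abstainers not observed: q(1 − r) / [q(1 − r) + (1 − q)L]

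Example 1 (q = 15%, r = 60%, L = 5%): 0.15 × 0.40 + 0.85 × 0.05 = 0.0600 + 0.0425 = 10.25%, against 5.0% under the restriction.

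Example 2 (q = 10%, r = 50%, L = 5%): 0.10 × 0.50 + 0.90 × 0.05 = 0.050 + 0.045 = 9.5%, against 5.0%.

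Across q = 5–15%, r = 30–70% and L = 2–5%:

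| Quantity | Lowest | Highest |
|---|---|---|
| All treated smokers | 3.4% (q 5%, r 70%, L 2%) | 14.75% (q 15%, r 30%, L 5%) |
| Endline smokers only | 2% | 5% |
| Abstainers not observed | 24% (q 5%, r 70%, L 5%) | 86% (q 15%, r 30%, L 2%) |

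**Comparison of conditions.** Take two conditions with q = 5% and q = 15%, and r = 50% and L = 3% in both.
- First: 0.05 × 0.50 + 0.95 × 0.03 = 5.35%.
- Second: 0.15 × 0.50 + 0.85 × 0.03 = 10.05%.
- The 6-month difference is 4.7 points in all treated smokers. Under the restriction it is 3% against 3%, because L was set equal.

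**Can imputation repair it?** In Example 1, counting every uncalled quitter as relapsed gives 0.85 × 0.05 = 4.25%. Counting every one as abstinent gives 0.15 + 0.0425 = 19.25%. The data could not narrow that interval.

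**The case against.** The strongest reply is that the exclusion is inferred. The article never says that patients abstinent at the first call are dropped, and it never dates the self-report. The phrase could simply restate the entry cohort: people who smoked when they received BISC. The stated aim of long-term effectiveness and the intent-to-treat commitment both fit that intention. Table 2 also places telephone callbacks at earlier periods, so a patient could have reported smoking before the end-of-intervention call. This part stands: the timing is open, and a reader who infers an explicit rule excluding quitters goes further than the text. It does not remove the point, because neither the intent-to-treat statement nor Table 2 says who is called at 6 months, and the one sentence that does so most naturally points to the call just described.

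A reader might also infer that differences between conditions in early quitting disappear from the trial. The article does not support that. The first call records smoking status, and Table 2 marks abstinence at mid-term and endline, so early quitting is still measured. What would be lost is whether it persists to 6 months.

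The illustrative figures do not show that the defect exists. They rest wholly on assumed rates, and the restricted figure is just the assumed late-quit rate returned. Finally, both calls are limited to patients who received BISC. That is a separate selection, and this point neither depends on it nor resolves it.

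**Conclusion.** The point holds as a defect in a stated follow-up rule, conditional on its most natural reading. Applied that way, 6-month 7-day abstinence measures only quitting after endline among patients still smoking at endline, and sustained quitters are missed. The downward bias has no knowable size from the article. Under the assumed ranges, 24% to 86% of 6-month abstainers would go unobserved, and the lead example gives 10.25% against 5.0%. If self-report was meant as status at the index visit, there is no bias and only the wording is at fault.

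The outcome is secondary. The primary outcomes and the sample size concern clinician behaviour and are unaffected. The sentence should still be changed before the calls begin, because the loss cannot be repaired afterwards and the correction is cheap.

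**What to change.** Define smoker status once, at the index visit, and replace the sentence on the 6-month survey with something like: *The 6-month survey will contact every patient in the end-of-intervention call cohort, regardless of the smoking status reported at that call; this cohort is the denominator for 6-month abstinence.*

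If the self-report condition was meant to remove patients wrongly recorded as smokers, the first call should ask about smoking at the index visit as a separate item from current smoking.

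The cost is one sentence and the additional 6-month calls to patients abstinent at endline. If index-visit status was always intended, there are no additional calls.
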